### Medico-economic evaluation

This first economic evaluation of the innovative diagnostic strategy of PE follows the recommendations from the French national health authority and the CHEERS statement for single-trial-based studies [21].

Given the non-inferiority hypothesis, the primary analysis assumes that the modified diagnostic strategy is either dominant (cheaper and equally or more effective) or decrementally cost-effective (cost-reducing and possibly TE event increasing below the upper bound of the 95% two-sided CI of the incidence rate ratio of TE events) [22, 23]. The perspective of the analysis is the healthcare system and the time horizon is 3 months. Resources will be collected prospectively at the patient level using the study case report form supplemented by data from the hospital claims database for the entire duration of the study period. Costs for the index admission and in-trial follow-up period are assessed using a combination of resource-based and event-based methods. In-hospital resource utilization will be described based on diagnosis and procedural codes and length of stay for the entire duration of the index admission and subsequent hospital stays. Out of hospital resources will be estimated from the CRF and patient interviews during the follow-up visits. We will collect information on ED visits, consultations, medications, and imaging laboratory tests. Out of hospital resources will be valued using the latest price/tariff schedule. In view of the short duration of this study, costs and benefits are not discounted. The economic evaluation will use the difference in the safety of each strategy as the effectiveness criterion in accordance with previous studies [24]. The analysis is based on the entire population of patients included in the trial.

The unit of analysis is the patient. Costs will be presented as means with 2.5 to 97.5% bootstrapped intervals. Between-group comparisons of costs will be performed using the bootstrap *t*-test. A joint comparison of costs and effects will be performed by nonparametric bootstrapping with 1000 re-samples and the probabilities of better/worse performance of modified diagnostic algorithm and higher/lower costs will be determined.

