The primary endpoint is the failure proportion of the diagnostic strategy, defined as a diagnosed thrombo-embolic event at 3 months follow-up (either a PE or a deep venous thrombosis), among patients in whom PE was initially ruled out. Exclusion of PE in the ED is done upon a negative D-dimer result or negative CTPA or negative V/Q scan in both groups. The primary criterion of thrombo-embolic event will be based on an objective diagnosis of DVT on Doppler ultrasonography, an intraluminal defect on CTPA, or a V/Q lung scan with a reported high probability. To confirm the occurrence of the primary endpoint, all files with evidence of thrombo-embolic event collected by the local investigator of each center will be independently reviewed by an adjudication committee of three experts, emergency physicians, blinded one to each other, and blinded to the study period. The adjudication committee will also review cases of death with no evidence of thrombo-embolic event and will adjudicate the death as likely related to a PE or not. Adjudication of a PE-related death will follow the recommendations of Tritschler et al. [19]. The review process includes analysis of all medical files of the patient from inclusion to follow up, including reports of any imaging study.

Secondary endpoints include:
CTPA or V/Q scanAnticoagulant therapy administrationLength of stay in the ED (hours)Admission to the hospital following ED visitAll causes re-hospitalization at 3 monthsDeath from all causes at 3 monthsDiagnosed pulmonary embolism at 3-month follow-up, excluding the isolated sub-segmental pulmonary embolism, among patients in whom PE has been initially ruled outPulmonary Embolism Probability Score (PEPS)3-month total cost and cost-effectiveness (cost per major adverse event averted)

Details of PEPS are reported in Table 3 [18].

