Since this is a non-inferiority study, analysis of the principal criterion will be performed on the per-protocol population (patients without major protocol deviation as no respect of selection criteria, no respect of strategy assigned by randomization, missing values for the principal criteria, or other major protocol deviation identified during data review before freezing of the data base). A sensitivity analysis will be performed on the intention-to-treat population (all randomized patients, except those that withdrew consent). Given the rare occurrence of a thrombo-embolic (TE) event, a generalized linear regression mixed model with Poisson distribution (log link) will be performed (Poisson model for proportions), taking into account a random effect for each center and considering period and strategy-by-period interactions as fixed effects. The decision rule will be based on the upper bound of the 95% two-sided CI of the incidence rates ratio of TE events. Any missing value will be considered as a failure. Secondly, sensitivity analysis will be performed using the 95% two-sided CI of the difference of percentage of TE events between groups. If the upper bound of the CI is above 1.35% of the difference, the inferiority hypothesis of the intervention group will be rejected. Secondary criteria will be compared between groups on the intention-to-treat population and under the superiority hypothesis. The proportions of irradiative imaging, of introduction of anticoagulation regimen, of hospital admission following the ED visit, of all causes of hospital readmission at 3 months, and of all-cause death at 3 months will be compared between groups by using generalized linear regression mixed models with Poisson distribution (log link), taking into account a random effect for each center and considering period and strategy-by-period interaction as fixed effects. If the number of events is sufficient, generalized linear regression mixed modeling with Bernoulli distribution (logit link) will be performed. The proportion difference between groups and its 95% CI will be calculated.

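### The safety limit for calling MODS decrementally cost-effective is the trial's own confidence bound and excludes no result, and the economic effect measure and population do not match the safety endpoint

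*Protocol article*

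**What the plan says.** **The classification.** The Medico-economic evaluation section starts from an assumption: "Given the non-inferiority hypothesis, the primary analysis assumes that the modified diagnostic strategy is either dominant" (cheaper and at least as effective) or decrementally cost-effective. It describes the second case as "cost-reducing and possibly TE event increasing below the upper bound of the 95% two-sided CI of the incidence rate ratio of TE events". It gives no numerical limit and does not mention the 1.35-point margin of the Sample size calculation section.

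**The same bound in the main analysis.** The Statistical analysis plan section states: "The decision rule will be based on the upper bound of the 95% two-sided CI of the incidence rates ratio of TE events". It gives no margin on the ratio scale. The 1.35% margin appears there only for the difference in percentages, as a sensitivity analysis.

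**The effect measure.** The list of secondary endpoints under Objectives and outcomes has "3-month total cost and cost-effectiveness (cost per major adverse event averted". The Medico-economic evaluation section says instead: "The economic evaluation will use the difference in the safety of each strategy as the effectiveness criterion". Its classification speaks of thrombo-embolic (TE) events.

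**The population.** For the economic evaluation: "The analysis is based on the entire population of patients included in the trial". The primary endpoint, under Objectives and outcomes, counts TE events only in patients whose PE was excluded at the index visit: "among patients in whom PE was initially ruled out. Exclusion of PE in the ED is done upon a negative D-dimer result". For the main analysis, "analysis of the principal criterion will be performed on the per-protocol population".

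**The concern.** A safety limit has to be set independently of the result it judges. Here it is the upper end of the interval around that result. An estimate cannot lie above the upper end of its own interval, so the limit cannot be crossed. A larger observed ratio also brings a larger bound, so the limit becomes more lenient as safety worsens.

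Cost-effectiveness is a named aim of the trial (end of the Background) and a listed secondary endpoint. A strategy that is cheaper but misses clearly more events than the plan tolerates would still fit the description of decrementally cost-effective.

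The second difficulty is the denominator and numerator of any cost-effectiveness ratio. Major adverse event is not defined in the article and is used nowhere else in it. The safety endpoint is defined in a subset of the patients on whom the economic analysis is run, and the article does not say how a patient with PE diagnosed at the index visit enters the effect count.

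**Working it through.** **Inputs.** From the Sample size calculation section: control failure rate 0.5%, margin 1.35%, one-sided alpha 2.5%, power 80%, N1 = 857, final size 700 per group. The event counts below are illustrative assumptions; clustering and period are ignored.

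**1. The plan's own figure, to fix the scale of the margin.** For equal rates and an absolute margin,

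n per group = 2 × 0.005 × 0.995 × (1.960 + 0.842)² / 0.0135² = 428.5, so 857.0 in total.

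This reproduces N1 = 857. The 1.35% is therefore an absolute difference in percentage points. At the planned control rate it corresponds to 0.5 + 1.35 = 1.85%, a ratio of 1.85 / 0.5 = 3.7. The plan does not state that ratio as a limit.

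**2. The economic condition.** With a control failures and b intervention failures in 700 patients each:

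- ratio = b / a
- upper bound = (b / a) × exp(1.96 × √(1/a + 1/b))

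The exponential factor is always greater than 1, so the ratio is always below the bound.

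**3. The fixed margin, for comparison.** Upper bound of the difference = (p₂ − p₁) + 1.96 × √(p₁(1 − p₁)/700 + p₂(1 − p₂)/700), compared with 1.35 points.

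**4. Worked example, 3 against 15.** Ratio = 15 / 3 = 5. √(1/3 + 1/15) = 0.632, and exp(1.96 × 0.632) = 3.45, so the upper bound is 5 × 3.45 = 17.3. The difference is 12 / 700 = 1.71 points, already beyond the margin before any interval is added. Its standard error is 0.60 points, so the upper bound is 1.71 + 1.18 = 2.89 points.

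| Control v MODS failures | Ratio | Upper bound of ratio (the plan's limit) | Meets the limit? | Upper bound of difference (points) | Below 1.35? |
|---|---|---|---|---|---|
| 4 v 4 | 1.00 | 4.00 | yes | 0.79 | yes |
| 3 v 15 | 5.00 | 17.3 | yes | 2.89 | no |
| 4 v 13 | 3.25 | 9.97 | yes | 2.43 | no |
| 4 v 20 | 5.00 | 14.63 | yes | 3.64 | no |
| 4 v 35 | 8.75 | 24.62 | yes | 6.14 | no |

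The four rows with 4 control failures show the limit rising from 4.00 to 24.62 as MODS failures rise. In the last row it corresponds to a MODS failure rate of 24.62 × 4 / 700 = 14.1%. Even with equal counts, the limit of 4.00 exceeds the ratio of 3.7 that the margin implies.

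**5. Effect measure and population side by side.**

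| Section | Effect | Population |
|---|---|---|
| Objectives and outcomes, secondary endpoints | major adverse event averted | not stated |
| Objectives and outcomes, primary endpoint | TE event at 3 months | PE initially ruled out |
| Statistical analysis plan, main analysis | TE event, rate ratio | per protocol |
| Medico-economic evaluation | TE event in the classification; difference in safety as the criterion | all included |

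A ratio and a difference are two scales of one outcome and can coexist. What does not agree is the event (TE or major adverse event) and the population. In the cheaper, more-events case that the section expressly allows, no event is averted, so a cost per event averted has to be re-expressed before it can be read.

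**The case against.** **The section sets no pass/fail test.** It assumes a classification under the non-inferiority hypothesis. If non-inferiority failed, that premise would fall away. This stands: the point concerns a description in a secondary analysis. It does not fully answer the concern, because the section never makes the label conditional on non-inferiority having been shown.

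**Harm would be visible elsewhere.** The main analysis is separate, and the bootstrap is to report the probabilities of better or worse performance and of higher or lower cost. This also stands. A reader might infer that any cost saving earns a favourable label however many events are missed. The document does not support that: an excess would appear in both places, and MODS can still fail on cost.

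**The bound can be exceeded in places.** Single bootstrap re-samples can exceed it (about 3% to 9% in illustrative counts), as in principle could an estimate from a different population. True, but the plan attaches no rule to either.

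**The phrase is inherited.** The Statistical analysis plan section also names the ratio bound without a margin. That is so, but the economic section would still have to cite a fixed limit once one is given.

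**The conflict in effect measure is mostly wording.** Safety has a meaning in the article, and a condensed article may leave the definition of major adverse event to the full protocol. In part this stands. What remains is that the terms and populations printed here disagree. A reader might go further and infer that PE found by index imaging would count as an adverse event, so that fewer scans would look like fewer events. No section says so, and the text is equally compatible with counting only later failures over all included patients.

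**Conclusion.** The point holds in limited form. As written, the safety half of the decrementally cost-effective description is empty: every estimate meets it, including 3 against 15 failures in 700, where the excess of 1.71 points is beyond the 1.35-point margin. That the estimate lies below its own bound follows from how an interval is built and needs no assumption. The sizes shown rest on illustrative counts and on crude intervals that ignore clustering and period.

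The mismatch in effect measure is real but narrower: an undefined major adverse event against TE events, and all included patients against those with PE ruled out.

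No sample-size figure and no part of the primary analysis changes. It is worth correcting because cost-effectiveness is a stated aim and the needed margin is already in the plan.

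**What to change.** 1. In the Medico-economic evaluation section, replace the confidence-bound condition. Call MODS decrementally cost-effective only if costs are lower and the upper 95% bound of the difference in failure proportion (MODS minus control) is below 1.35 percentage points. State the direction explicitly, because the sensitivity-analysis sentence in the Statistical analysis plan section rejects inferiority when the bound is above 1.35%. Say which population supplies the bound. The margin was set for the primary endpoint, and counting over all included patients would make the difference somewhat smaller.
2. In that section and in the secondary endpoint list, use one effect measure: adjudicated 3-month diagnostic failure counted over all included patients, with PE diagnosed at the index visit counted as non-failure.
3. When MODS is cheaper with more failures, report cost saved per additional failure.

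The cost is a few sentences in the protocol and the economic plan, with no new data. The small downside is that the favourable label can now be missed.

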### Ethics and dissemination

All eligible ED patients will be informed about the study by an information form in participating centers. The treating physician or the local investigator will explain the rationale and objectives of the study. An information note will be given to him/her, and he/she will be able to discuss the study with the physician or local investigator or research assistant. In France, since this is a cluster randomized trial with minimal risk and constraints, if a patient does provide freely-given oral consent, he/she can be included in the study. In addition, the investigator will specify in the person’s medical file the person’s participation in the research and the procedures for obtaining his/her oral consent. In Spain, signed informed consent from the patient will be sought.

This trial has been accepted by an institutional review board (IRB) in both France and Spain: Comité de protection des personnes Ile de France XI and Comité de Ética de la Investigación con medicamentos del Hospital Clínic de Barcelona.

Authorization from Agence Nationale de Sécurité du Médicament and Comité National Informatique et Liberté was also obtained before the start of the trial. There is no need of a data and safety monitoring board as this research is classified as “minimal risk”.

All modifications of the protocol will be shared with the relevant IRB for approval. The URC-Est clinical research platform and primary investigator will have access to the final dataset. Raw unidentified data can be shared for research purposes upon request after agreement with the sponsor and the primary investigator. The results of the trials and all potential ancillary or post-hoc analysis will be shared by communication in national congress and publication in peer review journals.

## Trial status

ClinicalTrials.gov Identifier: NCT04032769.

Recruitment status: Recruiting.

First posted: July 25, 2019.

Last update posted: November 19, 2019.

Study start date: October 1st 2019.

Expected study completion date: June 2020.

Protocol version: 2.1, 02/29/2020.

## Data Availability

A complete statistical analysis plan is available as an appendix. The trial dataset will be made available upon request to the authors or clinical research unit.
